### Secondary outcomes

#### Feasibility outcomes

Tracking data from our purpose-designed text message software will provide data on intervention delivery (i.e., number and type of text messages sent) and intervention engagement from participants (i.e. prompted text message replies from participants, unprompted text messages from participants, proportion of goal checks responded to and achievement of weekly behavioural goals). The number and duration of tailoring interviews attempted and completed is also tracked.

#### Acceptability outcomes

Data collected via a self-completed paper questionnaire at six months will assess participants’ recall of the number of texts received in the past week, their treatment of text messages after receipt (read and stored/read and deleted/deleted without reading) and categorical ratings of satisfaction (five categories ‘not at all satisfied’ to ‘extremely satisfied’) with GHSH and ratings of usefulness (five categories ‘not at all useful’ to ‘extremely useful’) for GHSH overall and specifically for support for achieving their behavioural and weight loss goals. In addition, participants are asked to write a one sentence, qualitative description of the GHSH intervention and are invited to complete a telephone interview (approximately 10 minutes) involving open-ended questions regarding intervention usage, satisfaction and potential program improvements.

#### Proposed mediators

The proposed mediators relating to the skills targeted in the GHSH intervention are measured at each assessment via paper-based questionnaire.

*Outcome expectancy for physical activity:* is assessed using participants ratings on a five-point Likert scale (1 = ‘strongly disagree’; 5 = ‘strongly agree’) of the likelihood of seven positive outcomes of regular physical activity (i.e., more energy; improved mental wellbeing; lower stress levels; increased confidence; feeling good immediately after exercise) and four negative outcomes (i.e., possible injury; sore muscles or joints; feeling tired; having less time to do other things). As suggested by Rodgers and Brawley [60], the specific physical activity outcomes were determined from previous cross-sectional evidence on the common positive outcomes [61] and negative outcomes [62,63] of regular physical activity.

*Outcome expectancy for diet:* items were adapted from Zunft and colleagues [64] who reported on the main perceived benefits of healthy eating among European adults. The negative outcome expectancies for diet were based on previous qualitative studies on perceived barriers and outcomes of weight loss [62,63]. Participants rate on a five-point Likert scale (1 = ‘strongly disagree’; 5 = ‘strongly agree’) the likelihood of five positive outcomes of healthy eating (i.e., weight loss; better control over weight; prevention or control over diseases; more energy; improved physical health) and four negative outcomes (i.e., feeling hungry; costing more; missing out on my favourite foods; not feeling comfortable in social situations).

*Satisfaction with outcomes for physical activity and diet:* based on the methods of Courneya and colleagues [59], this study uses one question for each outcome expectancy item to explicitly measure satisfaction of experiencing each physical activity outcome (e.g., I am satisfied that my current level of exercise improves my mental wellbeing) and dietary outcome (e.g., I am satisfied that my current diet has helped me to lose weight). The response scale consists of a five-point Likert scale (1 = ‘strongly disagree’; 5 = ‘strongly agree’).

*Self-regulation for physical activity and diet:* are measured using 20 modified items from Petosa’s [65] original 43-item questionnaire. This original questionnaire assesses the use of self-regulation strategies to support physical activity adoption and maintenance [65] and has been used successfully to detect change in physical activity self-regulation (overall α = 0.88; subscales α = 0.82 – 0.96). Self-regulation for diet is measured using a scale of 19 items that were also adapted from Petosa [65] covering self-monitoring, goal setting, reinforcement, time management, and relapse prevention. Each item asks how often the strategies were used in the last month on a five-point Likert response scale (1 = ‘never’; 5 ‘very often’).

*Self-efficacy for physical activity:* is measured using a 5-item scale with good internal consistency (α = 0.82) [14] and two-week test-retest reliability (r = 0.90) [66]. Seven items asks about confidence to engaging in regular physical activity under different scenarios (from 1 = ‘not at all confident’ to 5 = ‘extremely confident’).

*Self-efficacy for diet:* is measured across seven items with an adapted version of a diet barrier self-efficacy scale [67] that asks about confidence to eat a healthy diet under different scenarios (from 1 = ‘not at all confident’ to 5 = ‘extremely confident’).

*Social support for physical activity and diet*: is measured using a shortened version of the Social Support for Diet and Exercise Scale [68]. The original measure has good test retest reliability (r = 0.55 to 0.86, p < 0.001) and internal consistency (α = 0.61 to 0.91) [68]. The modified version includes 10 items each for diet and physical activity regarding frequency of support received in the past month (1 = ‘never’ to 5 = ‘very often’) from friends, family, or household members.

*Perceived environmental opportunity for physical activity:* are measured using an 8-item version of the International Prevalence Study on Physical Activity – Environmental Module [69]. The questions were modified slightly to suit the Australian population (e.g., sidewalks are now referred to as footpaths). Participants respond to statements about: access to shops, public transport and recreational facilities; presence of footpaths; crime and traffic safety; social environment; and, aesthetics of their neighbourhood (defined as 10–15 minute walk from home) on a five-point scale (1 = ‘strongly disagree’; 5 = ‘strongly agree’). This scale has shown good test retest reliability in Swedish [70] and Japanese [71] samples.

*Perceived environmental opportunity for diet:* The 8-item measure used in this study was modelled on the existing measures of food choice and affordability [72] and perceived availability of healthy foods in neighbourhood items [73], with additional items that evaluated neighbourhood takeaway perceptions. Neighbourhood is defined as 10–15 minute walk from the participant’s home and the response scale consists of a five-point scale (1 = ‘strongly disagree’; 5 = ‘strongly agree’).

#### Moderators

Proposed moderators of intervention outcomes that will be considered are: demographic characteristics (i.e. age, gender, education status, relationship status, cultural background, employment status); health status (i.e. chronic disease diagnoses prior to GHS enrolment, need for medical clearance for GHS enrolment); pre-intervention weight loss and behaviour changes (i.e., during the initial GHS); and, self-selected dose of GHSH text messages (including total frequency and frequency by types of text messages).

#### Costs of intervention delivery

These costs are tracked systematically in terms of personnel time and direct delivery costs. Costs are tracked for all intervention-related tasks, including: sending text messages; conducting tailoring calls (call costs and personnel time for preparation, attempts and successful calls); entering data into software for tailoring text messages; and, manually triggering replies to behavioural goal checks that are not recognised by the software.

### Statistical analysis

#### Intervention effects

Data will be analysed using intention-to-treat principles (i.e., participants will be analysed according to their randomly assigned group, regardless of the amount of intervention received). Each primary outcome will be modelled using mixed linear models with random intercepts, the fixed effects of study group, time (6-months/12-months) and a group by time interaction and will adjust for baseline values and potential confounders. Depending on the distribution of the continuous, interval or categorical outcome an appropriate distribution (e.g. normal, log-normal, gamma, negative binomial, binomial) and link (e.g., identity, logit) will be used. These models will assess intervention effects at end-of-intervention (6-months), end-of-maintenance (12-months) as well as differences between end-of-intervention and end-of-maintenance. Potential confounders include baseline demographic, behavioural and health characteristics as well as pre-intervention weight loss and behaviour changes. Those variables associated with the outcome at p < 0.2 will be adjusted as potential confounders. Final models will include all these potential confounders or remove those that do not affect estimates to within ±20% if models show evidence of overfitting. Sensitivity of conclusions to assumptions regarding missing data will be evaluated by comparing results obtained using different techniques of handling missing data (completers analysis, covariate adjustment and multiple imputation).

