### Sample size

The estimated differences between groups in change in primary outcomes (and standard deviations) for this trial are based on the outcomes from the maintenance evaluation of the GHS from 6 to 12 months without ongoing contact (same as control group treatment in the current study) [34] and literature on change in anthropometric and behavioural outcomes during extended contact interventions [17,18,31]. This evidence shows that we can expect small, continued improvements in the GHSH group from baseline to 6 months and declines in the no contact control group. Based on this, the minimum differences of interest in changes between groups from baseline to 6 months for our primary outcomes are: 2 sessions/week of self-reported moderate-vigorous physical activity; 1 serve of fruit per day and 1 serve of vegetables per day; 2 kg body weight; and, 4 cm waist circumference. The sample size requirement was largely determined by self-reported physical activity (sessions/week) as this outcome required the largest number of participants. Allowing for an attrition rate of 20%, the targeted sample size of 106 participants per group (212 in total) is needed to provide a ≥90% power with 5% significance (two-tailed) to detect a between group difference in change of 2 sessions per week of moderate-vigorous physical activity (assuming a standard deviation (SD) of 5.7sessions/week [34] and pre-post correlation (r) of 0.70 [unpublished data]). It is estimated, based on previous evaluations of GHS [34, unpublished data], that this sample size also provides ≥90% power to detect minimum differences of interest in all other primary outcomes including fruit serves/day (assumed SD = 0.9, r = 0.40), vegetable serves/day (assumed SD = 1.5, r = 0.37), weight in kilograms (assumed SD = 16.5, r = 0.97) and waist circumference in centimetres (assumed SD = 13.5, r = 0.80); as well as our additional measures of physical activity (accelerometer-measured moderate-vigorous physical activity minutes/week (assumed difference = 60, SD = 147, r = 0.60) [75]); and dietary behaviours (FFBQ Total Index (assumed difference = 0.20, SD = 0.50, r = 0.70 [76]).

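### For outcomes modelled as normal, chiefly weight, the random-intercept model as described implies equal residual variance at 6 and 12 months; allowing it to differ is a cheap safeguard for the 12-month interval (minor)

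*Protocol article*

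**What the plan says.** Under Statistical analysis, Intervention effects, the protocol article states: "Each primary outcome will be modelled using mixed linear models with random intercepts". The fixed effects are study group, "time (6-months/12-months) and a group by time interaction and will adjust for baseline values and potential confounders". Baseline is therefore a covariate, and each participant contributes at most two outcome values.

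Three contrasts are named: "These models will assess intervention effects at end-of-intervention (6-months), end-of-maintenance (12-months) as well as differences between end-of-intervention and end-of-maintenance".

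The same paragraph lets the model follow the outcome: "an appropriate distribution (e.g. normal, log-normal, gamma, negative binomial, binomial) and link (e.g., identity, logit) will be used". It names no covariance term other than the random intercept, and does not say whether standard errors are model-based or robust. The stated sensitivity analyses concern missing data only.

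The Sample size section gives one SD and one pre-post correlation per outcome, for change from baseline to 6 months. It gives neither an SD nor a correlation for 12 months.

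**The concern.** A random intercept with one residual variance gives the two follow-up values a compound-symmetric covariance: equal variances and one covariance. The group effects at 6 and 12 months are then both given standard errors from an average of the two variances.

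That is harmless if the variances are equal. They may not be. Correlation with baseline can weaken as time passes, and the Background section describes continuing weight regain after interventions end, which makes diverging trajectories credible without proving them. If baseline-adjusted spread is larger at 12 months, the 12-month interval is too short and its test rejects too often, while the 6-month interval is too long and its test loses some power. The 12-month contrast carries the maintenance conclusion, and none of the stated sensitivity analyses would reveal the problem.

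**Working it through.** **Inputs from the Sample size section.** Self-reported activity: difference 2 sessions/week, SD 5.7, r 0.70. Weight: difference 2 kg, SD 16.5, r 0.97. Waist: SD 13.5, r 0.80. Fruit: SD 0.9, r 0.40. Vegetables: SD 1.5, r 0.37. Also 106 per group, 20% attrition, two-sided 5%, power at least 90%.

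**The plan's own figure.** The baseline-adjusted SD for activity is 5.7 × √(1 − 0.70²) = 4.07. Then n = 2 × (1.96 + 1.2816)² × 4.07² / 2² ≈ 87.1, so 88 completers per group, and 88 × 1.2 = 105.6, so 106. The stated size is reproduced with a baseline-adjusted SD, which is the scale used below.

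**What the common-variance model does.** Let v6 and v12 be the true baseline-adjusted variances and c their covariance. With complete data and equal groups:
- the model uses v̄ = (v6 + v12)/2 at both times;
- model SE ÷ true SE is √(v̄/v6) at 6 months and √(v̄/v12) at 12 months;
- for the difference between times the model uses 2(v̄ − c) = v6 + v12 − 2c, which is the true variance, so that contrast is unaffected.

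Coverage is 2Φ(1.96 × ratio) − 1.

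**Results by outcome.** The marginal SD is held constant, so residual SD = SD × √(1 − r²). Every 12-month r is an assumption.

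| Outcome | r at 6 m | r at 12 m (assumed) | Residual SD 6 m, 12 m | SE ratio 12 m | Coverage 12 m |
|---|---|---|---|---|---|
| Activity | 0.70 | 0.65 | 4.07, 4.33 | 0.970 | 94.3% |
| Waist | 0.80 | 0.75 | 8.10, 8.93 | 0.955 | 93.9% |
| Fruit | 0.40 | 0.35 | 0.82, 0.84 | 0.989 | 94.7% |
| Vegetables | 0.37 | 0.32 | 1.39, 1.42 | 0.990 | 94.8% |
| Weight | 0.97 | 0.96 | 4.01, 4.62 | 0.936 | 93.4% |
| Weight | 0.97 | 0.95 | 4.01, 5.15 | 0.896 | 92.1% |
| Weight | 0.97 | 0.92 | 4.01, 6.47 | 0.832 | 89.7% |

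Weight stands out because 1 − r² is small at r = 0.97: it goes from 0.0591 to 0.0975 when r falls only to 0.95.

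**Effect at 6 months.** Take 85 completers per group (106 × 0.8 = 84.8) and power = Φ(difference / (SD × √(2/85)) − 1.96 × ratio).
- Weight, 12-month r 0.95: ratio 1.151. Power goes from Φ(3.25 − 1.96) = 90.2% to Φ(3.25 − 2.26) = 84.0%.
- Activity, 12-month r 0.65: ratio 1.033. Power goes from Φ(3.20 − 1.96) = 89.3% to Φ(3.20 − 2.02) = 88.1%.

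**Simulation check.** REML fits, 1,500 runs per setting, 106 per group, each setting run with complete data and with about 10% missing at 6 months and 20% at 12 months. Ranges span those two cases; SE ratio is mean model SE divided by the empirical SD of the estimate.

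| True SD ratio 12 m/6 m | SE ratio 6 m (coverage) | SE ratio 12 m (coverage) | SE ratio, difference (coverage) |
|---|---|---|---|
| 1.0 | 0.98–1.02 (95%) | 0.98–1.02 (95–96%) | 1.00–1.02 (95–96%) |
| 1.2 | 1.10–1.12 (97%) | 0.91 (93%) | 0.97–0.99 (95%) |
| 1.5 | 1.24–1.28 (98–99%) | 0.83–0.87 (90–92%) | 1.00–1.02 (95–96%) |

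The formula gives 1.105 and 0.920 at a ratio of 1.2, and 1.275 and 0.850 at 1.5, in line with the simulation.

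**Baseline slope.** With constant marginal SD, weight slopes of 0.97 and 0.95 replaced by a common slope of about 0.96 add only (0.01 × 16.5)² = 0.03 kg² to variances of 16.1 and 26.5 kg². The variance term matters far more than the slope term.

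**The case against.** The strongest reply is that the article does not fix the constraint. Equal variance comes from a common residual variance, which is not stated; a random intercept is compatible with time-specific residual variances or robust standard errors. Such detail is commonly left to an analysis plan, which may exist and is not shown. This stands, and it rules out calling the passage an error. It does not remove the point, because the article names one structure and adds nothing to it, and the usual default of that structure is a single residual variance.

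A second reply is that gamma, negative binomial and binomial models let variance follow the mean, and a log-normal model lets raw-scale spread change with the mean. This also stands. Sessions, servings and accelerometer minutes may be modelled that way, so the point is confined to outcomes treated as normal, for which weight and waist are the natural candidates.

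A third is that nothing in the document says spread is larger at 12 months, and that weight is the most sensitive outcome while the sample size was driven by self-reported activity. Both are correct. Outside weight the effect is small under the assumed fall in correlation.

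A reader might infer that random intercepts force equal variance on every primary outcome, that the 12-month tests are invalid, or that the trial is underpowered at 6 months. The document supports none of these: the first goes beyond what it specifies, and the other two need 12-month variances that it does not give. At 6 months the error is in the conservative direction.

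**Conclusion.** The point holds in a limited form and is minor. It rests on four conditions: the outcome is modelled as normal, one residual variance is used, standard errors are model-based, and baseline-adjusted spread grows between 6 and 12 months. The first three are a natural reading of the text; the fourth is an assumption.

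Under them, weight is the one outcome where the 12-month interval could be noticeably too short: by 6% to 17% for an assumed 12-month correlation between 0.96 and 0.92. For the other four outcomes examined, the shortfall is below 5%. If the variances are equal there is no effect.

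**What to change.** Add one sentence to the analysis description, or confirm it in the analysis plan. For outcomes modelled as normal, allow the residual variance to differ between 6 and 12 months, either by an unstructured 2×2 covariance in place of the random intercept or by a random intercept with time-specific residual variances, and include a baseline-by-time interaction. For outcomes modelled with other distributions, use robust standard errors.

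The cost is one extra variance parameter and one extra slope, with about 170 completers (2 × 85). If the variances turn out equal, the conclusions do not materially change. Design, data collection and sample size are untouched.

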### Randomization

Once informed verbal consent was obtained, the participants underwent the GHSH baseline assessment and were randomized to one of the study groups. Participants were stratified based on their change in weight during the GHS (using the median GHS weight loss of 3 kg). Randomization was conducted using a randomization website (http://www.randomization.com), and allocation was conducted by a trained research assistant with no involvement in participant recruitment.

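### Adjustment covariates for each primary outcome are selected from the outcome data, and the conditional ±20% removal rule suits a randomised comparison badly

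*Protocol article*

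**What the plan says.** The protocol article, under Intervention effects, specifies a mixed linear model for each primary outcome with "the fixed effects of study group, time (6-months/12-months) and a group by time interaction and will adjust for baseline values and potential confounders". The candidates beyond the baseline value are given by category: "Potential confounders include baseline demographic, behavioural and health characteristics as well as pre-intervention weight loss and behaviour changes".

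Entry is decided by the trial data: "Those variables associated with the outcome at p < 0.2 will be adjusted as potential confounders". The final model then either keeps everything that entered or may "remove those that do not affect estimates to within ±20% if models show evidence of overfitting". Keeping all screened covariates is therefore the default, and removal is a conditional branch.

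The Randomization section says: "Participants were stratified based on their change in weight during the GHS (using the median GHS weight loss of 3 kg". In the analysis section this factor appears only among the candidates, as weight loss before the intervention. It is not a fixed model term.

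**The concern.** Randomisation already protects the group comparison from systematic confounding by baseline variables. Adjustment mainly serves precision, and may also help make missing data ignorable. The choice of covariate should therefore rest on how well it predicts the outcome, and is best made before the outcomes are seen.

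The p<0.2 screen at least looks at prediction. The ±20% rule does not. Removing a covariate moves the treatment estimate by roughly its coefficient times its chance imbalance between arms. A strong predictor that is well balanced barely moves the estimate and is dropped, although it is the kind that reduces residual variance. A covariate survives mainly because of chance imbalance. The threshold is also relative to the estimate, so it tightens as the estimate nears zero. And the rule can be applied only by comparing treatment estimates across models.

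At stake are precision and power for the primary comparisons if the removal branch is used, and the credibility of a primary estimate whose model was settled while that estimate was in view. In addition, the analysis need not reflect the stratified randomisation.

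**Working it through.** **Inputs from the article (Sample size).** A two-sided 5% test, power of at least 90%, a target group difference of 2 activity sessions a week, an SD of 5.7, a correlation of 0.70 between baseline and follow-up, 20% attrition, and 106 per group.

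**Reproducing the planned sample size.**
- Baseline-adjusted SD: 5.7 × √(1 − 0.70²) = 4.07.
- A two-sided 5% test with 90% power for a difference of 2 needs 88 per group.
- Multiplying by 1.2 gives 105.6, so 106 per group, as printed. Dividing by 0.8 would give 110.
- With 106 × 0.8 ≈ 85 completers per group, power is 89.3%.

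The printed figure thus rests on adjustment for the baseline value alone. The choice of further covariates does not change it.

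**Why the ±20% rule drops prognostic covariates.** With a true effect of 2, 20% is 0.4 sessions. Suppose 5 independent prognostic covariates together explain a share R² of the residual variance.
- Each standardised coefficient is 4.07 × √(R²/5): 0.58 at R² = 0.1 and 1.00 at R² = 0.3.
- The between-arm difference in a standardised covariate has SD √(2/85) = 0.153.
- To shift the estimate by 0.4 on its own, a covariate must be imbalanced by 0.4/0.58 = 0.69, about 4.5 SDs, at R² = 0.1. At R² = 0.3 it is 0.4/1.00 = 0.40, about 2.6 SDs.

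Useful covariates therefore rarely survive, even though their shifts accumulate as removal proceeds.

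**Simulation.** 2,500 runs per scenario, 85 completers per arm, one time point, normal outcome, 15 independent candidates of which 5 are prognostic. The number of candidates and R² are assumptions. Removal was read as backward deletion while the group estimate stays within 20% of its value in the full screened model, and was applied in every run. Results for a true effect of 2:

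| | R² = 0 | R² = 0.1 | R² = 0.3 |
|---|---|---|---|
| Mean SE, prespecified 5 | 0.635 | 0.603 | 0.532 |
| Mean SE, p<0.2 screen | 0.625 | 0.605 | 0.541 |
| Mean SE, screen then ±20% | 0.625 | 0.624 | 0.618 |
| Mean SE, baseline value only | 0.625 | 0.625 | 0.626 |
| Power, prespecified 5 | 87.1% | 90.4% | 96.3% |
| Power, p<0.2 screen | 87.0% | 88.5% | 94.6% |
| Power, screen then ±20% | 87.8% | 87.2% | 91.0% |
| Power, baseline value only | 88.4% | 87.6% | 88.2% |
| Covariates after screen, after removal | 3.00, 0.05 | 4.51, 0.15 | 6.18, 0.40 |

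- *Removal branch against the prespecified set.* SE ratio 0.624/0.603 = 1.03 and 0.618/0.532 = 1.16. Power is lower by 90.4 − 87.2 = 3.2 and 96.3 − 91.0 = 5.3 points. The actual spread of the estimates grows less: 0.627/0.604 = 1.04 and 0.584/0.529 = 1.10.
- *Screen alone.* SE ratio 0.605/0.603 = 1.00 and 0.541/0.532 = 1.02. Power is lower by 1.9 and 1.7 points. The mean estimate is 1.93 to 1.96 against a true 2, which is 2% to 4% towards zero.
- *Type I error.* Screen 4.7% to 5.5%; after removal 3.0% to 5.2%. The Monte Carlo error near 5% is √(0.05 × 0.95/2500) = 0.4 points.
- *Free choice of model.* A separate simulation (170 completers, 15 to 25 candidates, 6,000 null runs) gave 5.7% to 5.9% if either final model may be reported. Adding the baseline-only model as a third option in the first simulation gave 6.2% to 7.3%.

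**The case against.** The strongest reply is that the rule is written down in advance, with its entry threshold, its removal threshold and a condition for removal. Removal is not the default, and the screen never looks at the treatment estimate. All of this stands. A reader might infer post-hoc selection, a general loss of precision or an inflated false-positive rate, but the article does not support those readings. The default path keeps precision and holds type I error near 5%. Inflation arises only if the analyst may choose which model to report, and the article sets a condition rather than granting that choice.

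Second, the comparator above assumes that the 5 prognostic covariates are known. That is fair. A further simulation under similar assumptions (170 completers, 6,000 runs) compared the screen with a realistic fixed list of three. With 15 candidates the screen had 89.4% power, and the fixed list 88.2%, 89.0% or 90.2% when 0, 1 or 3 of its members were prognostic. With 25 candidates the figures were 88.4% and 88.2% to 90.3%. The fixed list therefore gains about two points at best and can do slightly worse than the screen. If no candidate is prognostic, the removal step loses nothing.

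Third, different covariates for different outcomes are not an error, since weight, diet and activity plausibly have different predictors. The full candidate list and the criterion for overfitting may be set in an analysis plan that is not shown, so their absence here is not counted.

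None of this defends the ±20% clause. It is a printed method, not an omitted detail, and a plan that follows it inherits the problem.

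**Conclusion.** The point holds in a limited form. The article fixes a prestated but data-driven covariate rule whose conditional removal step is poorly suited to a randomised comparison, and it does not guarantee the stratification factor a place in the model. Where the removal branch is used and the candidates are prognostic, the cost is modest: the ranges shown for R² 0.1 to 0.3. The p<0.2 screen alone is nearly harmless.

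These sizes rest on the assumed number and strength of candidates, independent normal covariates, a single time point and one reading of the ±20% rule. Severity is minor to moderate. The stated sample size is unaffected, and nothing here shows that the primary results would be invalid.

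**What to change.** Delete the ±20% removal clause. Before unblinded analysis, name a fixed covariate set for each primary outcome. It should always contain the baseline value of that outcome and the GHS weight-change stratum, plus a few baseline variables chosen for expected prognostic value. Age and gender, already listed under Moderators, are possible choices. The set may differ between outcomes. Report the model selected at p<0.2 only as a sensitivity analysis.

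The cost is wording. No new data are needed, because the Data collection section says that demographics and changes during GHS come from the earlier GHS evaluations, and the sample size stays as it is. The downside is that a short fixed list may miss some prognostic variables and so gain slightly less precision than the screen would.
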